#### **4.4 Investigational treatment**

*Product:* Gaseous nitric oxide

*Dose:* 80 ppm

*Dosing schedule:* Continuous

*Route:* Inhalation (non-rebreather HiOx® face mask)

*Treatment period:* Maximum 72 hours (may be discontinued earlier if patient recovers and no longer tolerates face mask)

The iNO will be supplied in cylinders that will be appropriately labelled.

#### **4.5 Expected duration of subject participation**

*Duration of study gas (iNO or room air placebo):* maximum 72 hours (may be discontinued earlier if patient recovers and no longer tolerates face mask)

*Expected total duration of hospitalization for severe malaria:* 5 to 7 days

*Follow-up (1st visit):* 14 days after admission

*Follow-up (2nd visit):* 6 months after admission

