## **4 TRIAL DESIGN**

### **4.1 Endpoints**

*Primary endpoint:* Daily rate of change of Ang-2

*Secondary endpoints:*

1. Clinical efficacy:
  - a. 48 hour and 14-day mortality
  - b. recovery times:
    - i. time to fever resolution
    - ii. time to sit unsupported
    - iii. time to hospital discharge
  - c. time to parasite clearance
  - d. incidence of recrudescence at day 14

2. Other biomarkers and genetic determinants of malaria disease severity
  - a. whole blood lactate level
  - b. biomarkers and genetic determinants of endothelial activation, inflammation and coagulopathy, to be determined
3. Neurocognitive outcome at 6 months after discharge

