***Secondary outcomes******Therapeutic efficacy***

We will examine the efficacy of adjunctive iNO treatment using established clinical and parasitological outcomes: in-hospital mortality, recovery times (time to fever resolution, time to sit unsupported, and time to hospital discharge), time to parasite clearance, incidence of parasite recrudescence at day 14 after hospital discharge. These are standard outcomes in other therapeutic trials for malaria[64, 81, 82]. Routine intensive

monitoring of vital signs, clinical assessments on at least a daily basis by physicians experienced in the management of severe malaria, as well as measurement of key laboratory parameters and parasite density will be performed to collect this data.

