***Secondary endpoints:***

***48 hour and 14-day mortality***

The CRF will document whether the patient was alive or deceased or lost to follow-up at 48 hours after admission, and at the 14-day follow-up visit.

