## **5 SELECTION AND WITHDRAWAL OF SUBJECTS**

### **5.1 Inclusion criteria**

1. Age 1-10 years

2. Positive malaria rapid diagnostic test in the presence of selected features of severe malaria.
3. Willing and ability to complete follow up schedules for the study – 14 day and 6 months after hospital discharge.

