### **8.3 Procedures for eliciting reports of and for recording and reporting adverse event and intercurrent illnesses**

SAE forms will be made available to the DSMB, ethics boards and regulatory authority according to their requirements, which differ between each body. Accordingly, all SAEs will be reported to MUREC and the Uganda NDA as soon as possible, but within 15 days of the event. Unexpected SAEs will additionally be reported to the DSMB chairperson, MUREC, NDA, Jinja Hospital REB (as soon as possible, but within 15 days of the event). Fatal and life-threatening unexpected SAEs will be reported to the DSMB chairperson, MUREC, NDA, Jinja Hospital REB as soon as possible, but within at most 7 calendar days. Finally, SAEs that are unexpected, related or possibly related to the study intervention, and suggest an increase in risk to study participants or others will also be reported to the UHN REB (Toronto).

All SAEs that occur during hospitalization will be reported as described above.

Regarding SAEs that occur after hospital discharge, reports will be issued as described above for events occurring up to day 14 of the study (i.e., after hospital discharge, out to 14 days post-enrolment).

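### The first follow-up visit, and with it the recrudescence sample, is timed from admission in one place and from discharge in others: day 14 or about days 19 to 21

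*Protocol*

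**What the plan says.** The protocol gives these time origins for follow-up:

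- **Section 4.5, visit schedule.** First visit "14 days after admission"; second visit "6 months after admission". The same section expects a hospital stay of 5 to 7 days.
- **Section 5.1, inclusion criterion 3.** The family must be willing and able to attend follow-up at "14 day and 6 months after hospital discharge".
- **Sections 4.1 and 7.1, endpoint lists.** "incidence of recrudescence at day 14", with no origin given.
- **Sections 4.1 and 7.1, therapeutic efficacy text.** "incidence of parasite recrudescence at day 14 after hospital discharge".
- **Section 4.9, case report form.** Recrudescence rests on a blood sample from the 14-day visit. Vital status is recorded "at 48 hours after admission, and at the 14-day follow-up visit".
- **Section 8.3, SAE reporting.** After discharge, reports continue to day 14 of the study, explained as "after hospital discharge, out to 14 days post-enrolment".
- **Sections 4.1, 4.9 and 7.1, neurocognitive outcome.** "Neurocognitive outcome at 6 months after discharge" in the lists, and the same origin wherever the text gives one.

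Time to discharge is listed as a secondary efficacy endpoint in sections 4.1 and 7.1, and section 9.1 compares it between arms.

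**The concern.** The schedule and the endpoint text give different days for the same visit, and recrudescence depends on one sample taken there. Staff who follow section 4.5 will sample on a different study day from staff who follow the endpoint text. A sample taken on the wrong day cannot be repaired in analysis, because parasite status on the intended day was never observed.

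The two readings also differ in quality as time origins. Admission and enrolment precede treatment, so treatment cannot affect them. Discharge follows randomisation, and its timing is an efficacy outcome here. If inhaled nitric oxide shortened the stay, a discharge origin would place the sample earlier after randomisation in the active arm than in the placebo arm. Part of any difference in recrudescence could then reflect different observation time.

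**Working it through.** The protocol states no power or expected rate for these endpoints, so there is no figure of its own to reproduce. The only numerical input is the expected stay of 5 to 7 days in section 4.5.

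**Day of the first visit, counted from admission**

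- Admission origin: day 14 for every child.
- Discharge origin: 14 + stay, so 14 + 5 = day 19 up to 14 + 7 = day 21.
- Relative delay: stay / 14, so 5 / 14 = 36% up to 7 / 14 = 50%.

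The stay is an expected range, so individual gaps will vary.

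**6-month visit**

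- Taking 6 months as 182.6 days: 5 / 182.6 = 2.7% up to 7 / 182.6 = 3.8%.

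**Difference between arms, discharge origin only**

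A difference in mean stay passes one for one into the mean time from randomisation to the sample. The protocol gives no expected difference. If it were 0.5 to 2 days (an assumption), the arms' windows would differ by 0.5 / 21 = 2.4% up to 2 / 19 = 10.5%. With equal stays the difference is zero.

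**Illustration for recrudescence only**

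The protocol gives no recrudescence risk. Suppose the risk by day 14 is p and the hazard is constant; both are assumptions. The risk over the longer window is then 1 − (1 − p)^((14 + stay) / 14):

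- p = 5%: 6.7% to 7.4%
- p = 10%: 13.3% to 14.6%
- p = 20%: 26.1% to 28.5%

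This shows how the choice of day could move the event rate in both arms. It does not estimate bias between arms and should not be carried over to mortality, since section 2.4 says mortality is concentrated in the first few days.

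**Which statements agree**

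- Section 8.3 counts from enrolment and so sits with the admission origin in section 4.5.
- Against them stand section 5.1 for both visits and the efficacy text in sections 4.1 and 7.1 for recrudescence.
- For 14-day mortality, section 4.9 counts 48 hours from admission and then refers to the 14-day visit. No statement times it from discharge.
- For the neurocognitive outcome, every endpoint statement that gives an origin uses discharge, and section 4.5 is the exception.

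**The case against.** The strongest reply is that this is a wording slip with a narrow reach. Most of its elements are right.

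- **Mortality.** A reader might infer that 14-day mortality has two competing windows. The protocol does not support that. The endpoint is never timed from discharge, and discharge is no usable origin for a child who dies in hospital. Section 9.1 also plans Kaplan-Meier curves and a Cox model for time to death. Section 9.5 censors the survival curves at last contact, so these analyses tolerate unequal follow-up. What stands is smaller: the binary 14-day comparison takes its status from a visit whose date is in doubt.
- **Safety reporting.** A reader might treat section 8.3 as a third conflicting origin, or as a gap in safety follow-up. It agrees with the admission reading. A cut-off for reports to oversight bodies need not coincide with an efficacy visit, and sections 5.3 and 8.4 separately require adverse events to be followed until resolution.
- **6-month test.** This is an assessment at one point in time, so no risk window is lengthened. A shift of 5 to 7 days is small.
- **Dependence on treatment.** It arises only under the discharge reading, and only if length of stay differs between arms.

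The reply does not remove the conflict for the first visit and for recrudescence. An inclusion criterion alone might be read loosely, but the efficacy text appears twice and expressly attaches the discharge origin to the endpoint.

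**Conclusion.** The contradiction is explicit and unresolved for the first follow-up visit and the recrudescence endpoint. Its size is 5 to 7 days, or 36% to 50% of the 14-day interval, resting on the protocol's own expected stay. If the discharge origin is used, the sampling day also depends on a post-randomisation outcome; how much this matters between arms depends on a difference in stay that the protocol does not state.

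14-day mortality is affected only through the shared visit. The 6-month visit carries the same inconsistency at 2.7% to 3.8%, which matters for consistency more than for inference. The stronger conclusion, that follow-up for mortality or safety depends on treatment as the plan stands, is not supported. The primary endpoint, Ang-2 on days 0 to 3, and the sample size do not depend on any of this. The point merits correction because sampling days, once mixed, cannot be put right later.

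**What to change.** 1. Choose one origin that treatment cannot influence for the day-14 visit, recrudescence and 14-day mortality. Admission or enrolment already appears in sections 4.5 and 8.3; randomisation would also serve. If randomisation is chosen, state whether 48-hour mortality, now counted from admission, moves with it.
2. Correct inclusion criterion 3 in section 5.1 and the recrudescence text in sections 4.1 and 7.1 to match, and add the origin to the endpoint lists.
3. Define 14-day mortality in section 4.9 as death by day 14 from that origin, using the date of death instead of status at the visit. The planned time-to-death analysis needs that date anyway.
4. State a single origin for the 6-month visit and use it in sections 4.1, 4.5, 4.9, 5.1 and 7.1.

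The cost is wording, with no extra visits or samples and no effect on the sample size. The change is best made before enrolment starts.

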#### **4.6 Description of stopping rules/discontinuation criteria**

##### ***Individual patients***

We distinguish between adverse events that will result in temporary discontinuation of the study gas with the possibility of re-challenge after return to normal levels, and adverse events that will lead to patient withdrawal from the study.

##### ***Temporary discontinuation of treatment***

Treatment with study gas (iNO or placebo) will be temporarily discontinued if the following adverse events occur:

- Methemoglobinemia
- Elevated inspired NO2 concentration
- Persistent hypoxemia
- Evolving respiratory distress
- Unexplained tachycardia
- Unexplained hypotension
- Any study drug related adverse event that, in the opinion of the investigator, makes it unsafe for the subject to continue

Details and operational definitions are provided in the SOP: *Discontinuation of study gas*.

Subjects may be rechallenged with study gas (iNO or room air) after metHb, SpO2, HR, or SBP return to normal levels after discontinuation of study gas (iNO or room air).

##### ***Permanent Discontinuation of treatment***

If a subject experiences any of the following events during the 3 day iNO delivery period the study gas should be permanently discontinued:

- Refractory methemoglobinemia
- Hemoptysis

- Acute kidney injury
- Any study drug related adverse event that, in the opinion of the investigator, makes it unsafe for the subject to continue
- Any study drug related adverse event that repeats upon re-challenge at the same or lower dose level
- At the discretion of the subject or guardian
- At the discretion of the Investigator, if deemed appropriate, for any reason

Patients meeting these criteria will have study gas removed, and will be continued to be monitored until resolution of the abnormality. When study gas is permanently discontinued, patient data will continue to be collected for primary and secondary trial endpoints, including daily bloodwork. These results will be included in an intention-to-treat analysis.

### ***Entire trial***

Halting rules temporarily suspend study enrolment until a safety review is convened.

The objective of this review will be to decide whether the study should continue per protocol, proceed with caution, be further investigated, be discontinued or be modified and then proceed.

Halting rules for this study will be:

1. Mortality in any sequential group of 10 patients above statistical upper control limit (6/10 patients = 60%).
2. Cumulative mortality in any of the arms of the trial in excess of the upper statistical threshold.

Justification for these statistical thresholds is given in Appendix 1.

Safety review, interpretation of results and decisions about discontinuation of the trial will be made by a Data and Safety Monitoring Board (DSMB), using the suggested guidelines given here. We do not propose that the DSMB be strictly bound by pre-specified criteria, because of the complexity of the trade-offs between safety, efficacy, and costs, and the possibility that new information will change considerations. Rather, consideration of stopping guidelines requires a reasoned judgment based on all information that is available at the time of data review.

#### **4.7 Accountability procedures, including placebo and comparators**

iNO will be compared head-to-head with room air placebo in a randomized, parallel group design. All patients will receive standard-of-care antimalarial agents and supportive therapy for their severe malaria. Treatment and placebo will be indistinguishable for participants, caregivers and health professionals. All patients will wear a mask and receive room air, with supplemental oxygen as needed, delivered via compressor. The treatment group will also receive iNO mixed with the air flow. The dilution will be such that there will not be a perceptible difference between treatment and placebo flow rates.

#### **4.8 Maintenance of the trial treatment randomization codes and procedures for breaking codes**

The need for continuous safety monitoring (NO and NO2 levels in inhaled gas, methemoglobin levels) requires the presence of an unblinded team. This team will consist of the trial manager and locum nurses to assist with night coverage. The randomization code will be kept in a locked cabinet accessible by the trial manager only. The code will be consulted at the point of randomization, at which point the iNO or room

air placebo will be started by the trial manager. The code will be used for the purpose of tabulating data for the DSMB review on a quarterly basis, and at the midpoint of patient enrolment. Data will be disaggregated by treatment arm, although the treatment received (iNO or placebo) will not be known to the DSMB (“Group A” and “Group B”).

Unblinding of individual patients may be required under exceptional circumstances if there are safety concerns. The Jinja pediatrician may request this information from the trial manager in the rare event that knowledge of study gas may influence patient care. The entire trial population will be unblinded after completion of enrolment. Statistical analysis will be conducted in a blinded fashion, with patients assigned to “Group A” of “Group B” by the trial manager.

We will assess whether blinding has been successful by asking key trial persons (caregivers, health professionals, outcome assessors) to guess patients’ treatments and compare the answers with the actual treatments[88]. Statistical differences from chance alone will be evidence that trial blinding was compromised.

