## PROTOCOL SUMMARY

**Title:** **Inhaled Nitric Oxide as Adjunctive Therapy for Malaria: a Randomized Controlled Trial**

**Background:** Severe malaria remains a major cause of global morbidity and mortality. While the use of artemisinin-based antimalarial therapy has improved outcomes in severe malaria, the mortality rate remains high. Adjunctive therapies that target the underlying pathophysiology of severe malaria may further reduce morbidity and mortality. Endothelial activation plays a central role in the pathogenesis of severe malaria, of which the angiogenic factors angiopoietin-1 (Ang-1) and angiopoietin-2 (Ang-2) have recently been shown to function as key regulators. Nitric oxide (NO) is a major inhibitor of Ang-2 release from endothelium and has been shown to decrease endothelial inflammation and reduce the adhesion of parasitized erythrocytes. Low-flow inhaled nitric oxide gas (iNO) is a US FDA-approved treatment for hypoxic respiratory failure in neonates. Based on compelling data on the efficacy of iNO in experimental cerebral malaria in animal models, coupled with the documented safety of iNO in clinical practice and trials for other diseases, we propose a randomized clinical trial of iNO for the adjunctive treatment of severe malaria in Ugandan children.

**Population:** 180 children 1-10 years old admitted to hospital with moderately severe and severe malaria; 90 treated with iNO (80ppm) and 90 with placebo (room air).

**Site:** Jinja Hospital Children's Unit (Jinja, Uganda).

**Study Duration:** 12-18 months (recruitment and acute outcomes); 6 additional months to complete neurocognitive testing of cohort.

**Study Participant Duration:** 3 days; follow-up neurocognitive testing after 6 months.

**Objective:** To determine the efficacy of inhaled nitric oxide for the adjunctive treatment of *P. falciparum* malaria.

Our *specific aim* is:

**To determine whether supplemental low flow inhaled nitric oxide gas (80 ppm) in addition to Ugandan Standard of Care treatment reduces levels of**

**angiopoietin-2 (Ang-2) from baseline in children with moderately severe and severe malaria compared to Standard of Care treatment alone.**

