##### ***Allocation concealment***

After informed consent/assent is obtained, a study site investigator will draw a sequentially numbered sealed opaque envelope. The investigator will sign and date across the seal then open it to reveal randomization arm (iNO or placebo). Hence, local investigators will be unaware of the allocated treatment until after the patient has been randomized. We will retain all envelopes and records for subsequent inspection by study monitors.

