|                                           | 30% change
(810 pg/mL/day) | 40% change
(1080 pg/mL/day) | 50% change
(1350 pg/mL/day) |
| 40                                        | 82%                                   | 97%                                    | 99%                                    |
| 50                                        | 66%                                   | 89%                                    | 98%                                    |
| 80                                        | 42%                                   | 60%                                    | 80%                                    |

Estimates from the Jinja Regional Hospital indicate that a minimum of 175 patients with moderately severe and severe malaria (excluding patients with SMA) are admitted annually. This implies that accrual of all patients to meet the required sample size will take approximately 12-18 months (180 patients with severe malaria).

At the interim analysis (midpoint of enrolment), we may perform a sample size re-calculation using the observed variance estimates, the observed means at each time in the placebo group, and the observed dropout rate (*a priori* estimate: 10%). Sample size may be increased if feasible and if suggested by this analysis at midpoint of enrolment.

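### Section 4.8 lets the whole trial be unblinded once enrolment ends, about six months before neurocognitive testing is complete, and nothing keeps testers or caregivers blinded after that

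*Protocol*

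**What the plan says.** - **Release of the code.** Section 4.8: "The entire trial population will be unblinded after completion of enrolment". No other condition is attached: not the end of follow-up, not database lock, and no list of who receives the allocations. The next sentence has the statistical analysis done blind, with arms labelled A and B by the trial manager.
- **Timetable.** The Protocol Summary gives the study duration as "12-18 months (recruitment and acute outcomes); 6 additional months to complete neurocognitive testing of cohort".
- **Endpoint.** Section 4.1 lists as a secondary endpoint "Neurocognitive outcome at 6 months after discharge", and section 7.1 repeats it. Section 9.1 analyses it as frequencies of deficit and as age-adjusted test z-scores.
- **Blinding claimed.** Section 4.2 calls the trial double-blind. Section 4.3(b) relies on a blinded team for all clinical assessments. Section 4.8 plans to test blinding by asking outcome assessors, among others, to guess the treatment.
- **Allocation step.** Section 4.3(a) says that after consent "a study site investigator will draw a sequentially numbered sealed opaque envelope" and opens it. Section 4.8 describes a code that only the trial manager can reach, and says: "The code will be consulted at the point of randomization".

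**The concern.** The code can be broken for everyone while one listed endpoint is still being collected. Neuropsychological testing of young children depends on how the tester engages and scores the child, and on the caregiver bringing the child back. Knowledge of the arm can affect both. The damage would fall on the children enrolled last, so the endpoint would mix blinded and unblinded assessments.

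This is the only endpoint that reaches beyond about two weeks, so it carries any claim about lasting benefit. The planned check on blinding would mean nothing for an assessor who already knew the allocation. Timing of code release is a matter that section 4.8 itself fixes, so this is a rule set too early, not a detail left for a statistical analysis plan.

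**Working it through.** **Inputs from the protocol**

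- Sample size 180, about 90 per arm (section 9.2).
- Accrual: "accrual of all patients to meet the required sample size will take approximately 12-18 months" (section 9.2).
- Admissions: "a minimum of 175 patients with moderately severe and severe malaria (excluding patients with SMA) are admitted annually" (section 9.2).
- Long-term visit at 6 months, counted from discharge in section 4.1 and from admission in section 4.5. Expected stay 5 to 7 days (section 4.5).
- Expected mortality about 20% (section 8.1).
- Planned dropout 10% (sections 5.3(c) and 9.2).
- First follow-up visit 14 days after admission (section 4.5).

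**Step 1. Reproduce the accrual period.** If every eligible child enrolled, 180 / 175 x 12 = 12.3 months. Eighteen months corresponds to 180 / 18 x 12 = 120 children a year. The stated range reproduces, with its lower end slightly optimistic.

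**Step 2. Share of 6-month tests outstanding when enrolment closes.** Assume uniform accrual over T months. Children enrolled in the last 6 months are still untested, so the share is 6 / T.

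| T (months) | Share | Of 180 enrolled | Survivors (x 0.8) |
|---|---|---|---|
| 12 | 6/12 = 50% | 90 | 72 |
| 12.3 | 6/12.3 = 49% | about 88 | 70 |
| 15 | 6/15 = 40% | 72 | about 58 |
| 18 | 6/18 = 33% | 60 | 48 |

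Counting from discharge instead of admission changes little: 51-52% at 12 months and 34-35% at 18 months. If the planned 10% dropout also applied to this visit (an assumption, since the protocol gives no separate rate for it), the survivors tested after release would be 0.9 x 48 = about 43 to 0.9 x 72 = about 65.

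**Step 3. Share of 14-day visits outstanding.** 14 days / 18 months = 2.6% and 14 days / 12 months = 3.8%, which is about 5 to 7 of 180 children.

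**Step 4. Does any other text protect the 6-month visits?**

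- The A and B labelling in section 4.8 covers the statistical analysis. It does not mention testers or caregivers.
- The blinded team in section 4.3(b) is set up against a second team that delivers and monitors the gas. That section does not say the separation outlasts a general release.
- The neurocognitive sections (4.1, 7.1, 9.1) refer to procedures held elsewhere and say nothing about blinding of testers.

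**Step 5. Effect of waiting.** Release after the last 6-month assessment moves from about month 12-18 to about month 18-24, which matches the Summary's own timetable. Sample size, significance level and power do not change.

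**The case against.** The strongest reply is that the sentence sets an earliest time and no date, and names no recipients. A release after the last 6-month visit would satisfy it. Section 4.3(b) promises blinded clinical assessment, and the neurocognitive procedures, which are not shown, may keep testers blinded. All of that is fair. A reader might infer that the plan makes the later assessments open-label; the text does not say so, and what it supports is a risk. The risk remains because the end of enrolment is the only condition stated, and it covers the entire trial population.

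The share in Step 2 is also an upper-range illustration. It assumes release on the day enrolment closes and even accrual, although section 2.6 describes transmission as seasonal. It also assumes that every survivor is tested, unless dropout is allowed for. The true share could be higher or lower, but under release at that point it cannot be zero, because the last child enrolled always has six months to go.

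Four wider readings are tempting and not supported:

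- *The primary result is compromised.* Ang-2 is a laboratory measure taken on days 0 to 3, so it is largely unaffected.
- *The 14-day outcomes are compromised.* They are death and a blood sample for parasite density. About 5 to 7 children are involved, and the Summary places acute outcomes in the same phase as recruitment.
- *Performance bias from the gas.* Study gas stops within 72 hours, long before the 6-month visit.
- *Allocation concealment is broken because the trial manager can see the list.* Section 4.3(b) keeps that person out of patient care, and no section gives them a part in deciding eligibility or obtaining consent. What stands is that sections 4.3(a) and 4.8 name different people and different documents for the same step.

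**Conclusion.** The point holds as a rule fixed too early. Section 4.8 permits allocations to be released while an assessor-dependent secondary endpoint is still being collected, and the protocol contains no safeguard for testers or caregivers. On the protocol's own accrual range, with uniform accrual and release at the close of enrolment, about a third to a half of the children would be tested after release. The harm is possible ascertainment bias and differential return on the neurocognitive outcome. It does not extend to the trial's primary conclusion. The difference between the two descriptions of allocation is a minor wording conflict and does not show that concealment failed.

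**What to change.** Replace the release sentence in section 4.8 with: *Allocations will be released only after the last 6-month neurocognitive assessment and database lock. If acute results are analysed earlier, allocations will be released only to a statistician who has no contact with participants, caregivers or neurocognitive assessors.*

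The cost is a delay of up to six months for the acute results, or the effort of running a firewall. The trial manager's existing uses of the code (tables for the safety board, mortality plots, emergency unblinding of individual patients) can continue as planned. The change has to be made before any general release, because blinding cannot be restored afterwards.

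Separately, reconcile sections 4.3(a) and 4.8 so that one allocation procedure is stated: who opens or consults what, and when. This is a wording change only.
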